*Random Allocation and Concealment:* Random allocation will be conducted by the Study Coordinator after baseline assessment completion; randomization will be stratified by suicide attempt history. The randomization scheme will be produced using Statistical Analysis System (SAS) PROC PLAN with a specified seed and random block sizes, prior to any recruitment and will be conducted by [name]. To ensure concealed allocation, participants will be designated by an identification (ID) number. ID numbers will only be forwarded to the Study Coordinator, who will randomly allocate participants based on the randomization scheme. In this way, only the Study Coordinator (not the participant, blind assessor, or other research personnel involved in data acquisition) will know condition assignment.

*Intervention:* Following the baseline assessment, up to 226 Veterans will be randomized to SHUTi (n = 113) or the educational website control (n = 113). These interventions will run for nine weeks.

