***Analysis Plan***

All analyses will assume a two-sided test of hypothesis and a significance level of 0.05, unless otherwise noted. Preliminary descriptive and graphical analyses (e.g., boxplots, scatterplots) will be used for data checking and visualization. Demographic and clinical characteristics (including but not limited to age, gender, PTSD, BDI-II scores, BAI scores, and the Life Experiences Survey for the six-month and one-year outcomes) will be compared between groups using t-tests, chi-square tests, Wilcoxon rank-sum tests or Fisher’s exact tests as appropriate to check randomization. Any variable that is found to be different between the groups at the p<0.10 level, and is a plausible potential confounder in consideration of the association under investigation, will be included as a covariate in the analyses described below. This includes an examination as to whether suicide risk variables will be included as covariates.

Given that the aim of the RCT is to test the efficacy of SHUTi, we will perform a per-protocol analysis such that those participants who do not have post-intervention data will not be included in the analysis. Additionally, we will perform a sensitivity analysis using the last value carried forward for those who drop out. This conservative contrast will give some insight into the effectiveness of the intervention and bolster the efficacy findings if they are consistent with the primary analysis.

Primary Aim, Hypothesis 1.1. The primary analyses will be the comparison between groups of the change in 1) insomnia symptom severity as measured by the ISI, 2) physical health as measured by the physical component of the Veteran’s SF-36, and 3) mental health as measured by the mental component summary score on the Veteran’s SF-36, from Time 1 to Time 2. Statistical inference regarding the difference between intervention groups will be based on the estimated coefficient for a group indicator variable in each of three analysis of covariance models with the change from Time 1 to Time 2 for each outcome serving as the dependent variable. Additional covariates will include the baseline value of the outcome to improve precision of the estimate, and any potential confounders discovered in the randomization check. To control for the three primary comparisons, the significance level will be set to 0.0167.

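### Primary-model covariates are picked by baseline tests at p<0.10 and the randomisation stratum is not fixed in the model: an undetermined model and a modest loss of precision

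*Protocol*

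**What the plan says.** The Analysis Plan in section IV.F of the Protocol compares the arms on demographic and clinical characteristics with significance tests. The candidates are open-ended: "including but not limited to age, gender, PTSD, BDI-II scores, BAI scores", with the Life Experiences Survey added for the later time points. The entry rule has two parts. The first is statistical: "Any variable that is found to be different between the groups at the p<0.10 level". The second is a judgement: "and is a plausible potential confounder in consideration of the association under investigation, will be included as a covariate". On suicide-related variables the plan goes no further than this: "This includes an examination as to whether suicide risk variables will be included as covariates".

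Primary inference rests on the "estimated coefficient for a group indicator variable in each of three analysis of covariance models". The covariates of those models are "the baseline value of the outcome to improve precision of the estimate, and any potential confounders discovered in the randomization check". On the error rate: "To control for the three primary comparisons, the significance level will be set to 0.0167".

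Under Random Allocation and Concealment, the Protocol states that "randomization will be stratified by suicide attempt history". Nothing in the document fixes that stratum as a term in any efficacy model. The analyses for Hypotheses 1.2 and 1.3 and for Exploratory Objective 1.4 follow the same methods, so the rule applies to them too.

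**The concern.** Allocation is random and concealed. Among those randomised, a baseline difference at p<0.10 is therefore a chance event, and it says nothing about whether the variable predicts the outcome. A strong predictor that happens to balance is left out, and a weak one that happens to differ can be let in.

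Three consequences follow.

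- **The model is not known in advance.** The list is open and the confounder judgement is made after the arms are compared. The covariate set could also differ between the three primary outcomes and between time points.
- **The stratum tends to be excluded.** Stratification balances attempt history by design, so a test for imbalance is the wrong gate for it.
- **Precision is lost.** When a balanced prognostic factor is omitted, the treatment estimate varies less than the model standard error says. Intervals are then too wide and the test rejects too rarely.

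**Working it through.** **Inputs from the Protocol.** 85 completers per arm, effect 0.6, two-sided alpha 0.05/3 = 0.0167 (Sample Size and Analysis Plan); entry threshold p<0.10; five candidates named for the Time 2 models (age, gender, PTSD, BDI-II, BAI).

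**Inputs assumed, because the Protocol gives none.** Attempt-history prevalence 20%; share of variance beyond baseline explained by the stratum (3–5%) and by three other baseline scores together (10–15%). Effects are in SD units of what remains after the baseline outcome is fitted. If baseline explains part of the variance, the Protocol's 0.6, set for a plain t-test, becomes larger in these units and the losses below shrink.

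**The plan's own power figure.** Standard error √(2/85) = 0.153; noncentrality 0.6 × √(85/2) = 3.91; critical t on 168 df = 2.417. Power is 93.1%, not the stated 80%. An effect of 0.5 gives noncentrality 3.26 and power 79.9%. That mismatch is a separate matter. Here it is the reason for showing both 0.6 (the stated effect) and 0.5 (where these inputs give 80%).

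**Chance entries.** With five independent candidates, the probability of at least one p<0.10 is 1 − 0.9^5 = 0.41, before the confounder judgement. Correlation among PTSD, BDI-II and BAI would change this.

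**Will the stratum be selected?** If attempt history is balanced among the 113 per arm randomised and about 25% then drop out at random, imbalance among completers has only about 1 − 85/113 = 0.25 of the variance that the test assumes. Its SD is half the nominal one, so passing p<0.10 needs a deviation of 1.645/0.5 = 3.29 SD, a chance of about 0.1%. Simulation gave under 0.3%.

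**Stratum alone, closed form.** If the stratum explains R², the true variance of the estimate is multiplied by (1 − R²), but the model standard error is not. At R² = 5% the standard error is overstated by 1/√0.95 = 1.026, and the actual type I error is 0.0131 against 0.0167. Power, stratum omitted versus fixed: 80.6% vs 82.2% at 0.5, and 93.7% vs 94.4% at 0.6.

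**Full rule, simulated** (5,000 trials per setting, 85 per arm, exact balance within strata; p<0.10 selection without the stratum, against a fixed model with stratum and scores):

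| Stratum + scores | Effect 0.5: rule vs fixed | Effect 0.6: rule vs fixed |
|---|---|---|
| 5% + 15% | 80.9% vs 88.2% (7.3 points) | 94.3% vs 97.2% (2.9) |
| 3% + 10% | 80.2% vs 84.4% (4.2) | 94.0% vs 95.9% (1.9) |
| 5% + 0% | 79.9% vs 81.2% (1.3) | 93.9% vs 94.7% (0.8) |

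Repeat runs agreed to within about one point. At 5% + 15% the rule's mean standard error was 0.153 against an empirical SD of 0.143–0.146, so 5–7% too large (0.153/0.146 = 1.05; 0.153/0.143 = 1.07). Its type I error was 1.0–1.2% against 1.67%.

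**The case against.** The strongest reply is that little is at stake. The most useful covariate, the baseline value of the outcome, is already fixed. The error made by the mechanical rule is on the safe side. At the stated effect, power stays well above 80% in every setting examined. Most of the loss comes from assumed prognostic scores that the plan was never obliged to include, and with scores of no prognostic value it is negligible. All of this stands, and it limits the size of the point.

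A second reply is that differences need not be chance here. The primary analysis drops participants without post-intervention data, with 25% attrition assumed, and the Protocol does not say whether the check uses everyone randomised or completers only. Among completers, differential dropout could unbalance the arms, attempt history included. This also stands: the statement that differences are chance holds for those randomised. It does not rescue the rule, because a significance screen is a poor guard against dropout imbalance and covariates named for prognostic value are a better one.

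A third reply is that covariate lists belong in a statistical analysis plan, which is not at hand. For the stratum taken alone that would be fair. But the Protocol states a selection rule, and a later plan that follows it inherits the fault.

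A reader might go further and infer that the rule inflates false positives or biases the primary result. The documents do not support that. Applied mechanically, the rule is conservative. The judgement step could in principle be used selectively, but nothing shows that it would be, and its effect was not simulated.

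**Conclusion.** The point holds as a matter of pre-specification and modest efficiency. The Protocol leaves the primary model undetermined until the arms are compared, selects covariates by imbalance, and does not secure the stratification factor a place in the model.

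Under the assumed prognostic strengths, the loss is about 2–3 points of power at effect 0.6 (roughly 93–95% against 95–97%) and 4–7 points at 0.5. The stratum alone, at 5% of variance, costs under 1 point at 0.6. The direction is firm if the covariates are prognostic; the size depends on strengths and a stratum prevalence that the Protocol does not give.

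Two stronger readings should be resisted. The rule does not leave the trial underpowered at its stated effect. Nor is omission of the stratum a large defect in itself, since most of the loss comes from leaving out other predictive scores when they happen to balance.

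**What to change.** Delete the p<0.10 rule. For every efficacy model, name the covariates now:

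- the baseline value of the outcome;
- the suicide-attempt-history stratum;
- a short list of Time 1 scores chosen for expected prognostic value and already collected under Table S1, for example BDI-II and PCL-5.

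Describe baseline characteristics by arm without using tests to choose covariates. If imbalance through dropout is a worry, say so and rely on the named covariates.

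The cost is a change of wording and a few degrees of freedom out of about 170. It needs no new data, visits or participants.

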**Protocol #: 17-0920**

**Project Title: Vets Sleep**

**Principal Investigator: [name].**

**Version Date: 10-18-18**

**I**. **Hypotheses and Specific Aims**:

**Specific Aim**: Determine the efficacy of a prominent computerized cognitive behavioral therapy (cCBT), called Sleep Healthy Using the Internet (SHUTi), for treatment of insomnia among Operation Enduring Freedom (OEF), Operation Iraqi Freedom (OIF), and Operation New Dawn (OND) Veterans. Efficacy will be evaluated using a two group (SHUTi vs. educational website control) longitudinal (four time points) randomized controlled trial (RCT) design.

*Objective 1.1*: Determine if there are significant differences in insomnia symptom reduction and physical and mental health functioning between participants in the two groups.

*Hypothesis 1.1*: Participants randomized to SHUTi will report a significant pre-intervention to post-intervention decrease in insomnia symptoms, and improvement in functioning compared to participants who are randomized to the educational website control.

*Objective 1.2 & 1.3*: Determine whether changes in insomnia symptoms and physical and mental health functioning are maintained six-months and one-year post-intervention.

*Hypothesis 1.2 & 1.3*: Participants randomized to SHUTi will report a significant pre-intervention to six-months and one-year post-intervention decrease in insomnia symptoms, and improvement in functioning compared to participants who are randomized to the educational website control.

*Exploratory Objective 1.4*: Determine whether SHUTi is associated with significant reductions in sleep diary parameters (i.e., sleep efficiency, sleep onset latency, wake after sleep onset) and key variables including suicidal ideation, depressive symptoms, anxiety, and post-traumatic stress disorder (PTSD)).

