*Educational Website Control:* The educational website control used in this RCT has been previously developed by University of Virginia researchers. When developing the educational website control, researchers conducted a thorough online review to determine what constituted “treatment as usual” for patient education websites targeting insomnia. Informed by this review, the educational website control was designed and includes the following: 1) content presented all at once; 2) treatment information about insomnia symptoms, diagnosis and differential diagnosis of insomnia, etiology, the natural history of insomnia and its prognosis, and cognitive-behavioral treatment strategies; 3) printable documents (including sleep diaries and insomnia severity assessments); 4) a FAQ section which provides answers to frequently encountered patient problems; and, 5) automated email prompts to encourage users to return to the site. Non-automated individual patient inquiry elements, such as forums and “ask the expert,” are not included as these can confound the obtained content (as different users may or may not receive helpful content, if anything at all). As indicated above, a detailed FAQ section is included, which parallels this type of content but in a more systematic way.

*Post-Intervention Assessment:* Following the intervention period, all allocated participants will be contacted to complete the post-intervention assessment. Participants will receive a phone call or email reminding them to complete the post-intervention assessment online via the web-based platform. The study team member coordinating the assessment will be blind to the participant’s group membership. To ensure that both the blind assessor and study participant do not gain information relevant to their group assignment, the blind assessor will remind the participant at the beginning of the reminder call to not discuss information about their web-based participation as this information may signal whether the participant received SHUTi or the educational website control. After each post-intervention assessment reminder, the blind assessor will be asked to record whether the participant broke the blind. Please see Table S1 for a list of all post-intervention assessments. Participants will be compensated $50 for the post-intervention assessment.

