**F. Data Analysis Plan:**

***Sample Size***

Power was based off of the nine outcomes comprising Specific Aim 1, Hypothesis 1.1. Given these nine outcomes (insomnia symptom severity based on the ISI, physical and mental component summary scores on the Veteran’s SF-36), a Bonferroni correction was used and we assume an alpha level of 0.0167. We additionally assume a two-sided test of hypothesis and used the two-sample t-test procedure in PASS v13.0.11 to calculate power. Using any pair power, and the Horn sequential procedure121-122 to control the familywise error rate, with a final sample of at least 170 completing the post-intervention assessment (85 per group), we have 80% power to detect an effect size of 0.6 (medium effect size) for each outcome. As we assume an attrition rate of 25%, 226 participants will be randomized to achieve at least 85 per group completing the post-intervention assessment.

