Hypothesis 1.2 and 1.3. A similar analysis will be performed for the above noted outcomes on the change from Time 1 to Time 3 and to Time 4 to determine persistence of group differences to six months and one year post intervention. Additionally, a sensitivity analysis will be performed utilizing a mixed-effects model and all available data, with estimation of the change from Time 1 to Times 2, 3 and 4. The sensitivity analysis will be evaluated for each hypothesis and if it is not consistent than the results for the specific hypothesis will be considered inconclusive.

Exploratory Objective 1.4. For the exploratory outcomes of sleep diary variables (sleep efficiency, sleep onset latency, and wake after sleep onset), risk for SDV (ASIQ), anxiety (BAI), depression (BDI-II), PTSD symptoms (PCL-5), the methods outlined above for the primary analyses will be utilized for the change from Time 1 to Time 2, Time 3, and Time 4.

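### The primary analysis set, called per-protocol, is really a completer set and does not match hypotheses stated for everyone randomised

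*Protocol*

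**What the plan says.** Under Analysis Plan (section IV.F), the protocol gives the efficacy aim as its reason and then defines the primary set: "we will perform a per-protocol analysis such that those participants who do not have post-intervention data will not be included in the analysis". The primary analyses are three ANCOVA models of change from Time 1 to Time 2 (ISI and the two SF-36 component summaries), each tested at 0.0167. Last value carried forward for dropouts is planned as a sensitivity analysis and described as conservative.

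For Hypotheses 1.2 and 1.3, a similar analysis is applied to change to Time 3 and Time 4. In addition, "a sensitivity analysis will be performed utilizing a mixed-effects model and all available data", and "if it is not consistent than the results for the specific hypothesis will be considered inconclusive".

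Section I words Hypothesis 1.1 for those assigned: "Participants randomized to SHUTi will report a significant pre-intervention to post-intervention decrease in insomnia symptoms", compared with those randomised to the control. Hypotheses 1.2 and 1.3 are worded the same way. Under Assessment & Intervention Procedures, "all allocated participants will be contacted to complete the post-intervention assessment", and the same procedure applies at six months and one year.

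**The concern.** A per-protocol set is normally defined by adherence. This one is defined by whether data exist. A SHUTi participant who opened no core but answered at Time 2 is included; one who finished all six cores but skipped Time 2 is excluded. The protocol itself expects the first kind: Table S1 places a questionnaire at Time 2 for SHUTi participants who did not complete all cores. The set therefore isolates neither treated participants nor all those randomised, and the efficacy rationale does not support it.

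Missingness that differs by arm is plausible from the design. The Risks section says SHUTi may increase tiredness through restricted time in bed. SHUTi cores open on a timed schedule, whereas the control content is available at once. Adding the item times in Table S1, the Time 2 battery takes 85 minutes for control participants, 115 for SHUTi participants, and 120 for SHUTi participants who did not finish all cores.

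At stake is whether the reported effect describes the randomised groups or only those who answered.

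**Working it through.** **Inputs from the protocol.** 226 randomised (113 per arm); 170 completers needed (85 per arm); 25% attrition assumed; 0-12% attrition in earlier SHUTi trials (Potential Scientific Problems); standardised effect 0.6; two-sided alpha 0.0167.

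**The plan's own figures.** 170 / (1 - 0.25) = 226.7, and 226 x 0.75 = 169.5, so 226 reproduces to rounding. 0.05 / 3 = 0.0167 reproduces.

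**How many are excluded.** At 25% attrition, 0.25 x 226 = 56.5, so about 56 people leave the primary analysis. At 12%, 0.12 x 226 = 27.

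**Time 2, missing SHUTi participants assumed to gain nothing over control.** The effect in all randomised is the completer effect times the share observed.
- 25% missing: 0.60 x 0.75 = 0.45 SD.
- 12% missing: 0.60 x 0.88 = 0.53 SD.

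A mixed model would not change this. Someone who leaves before Time 2 and never returns contributes only a baseline value, so the Time 2 contrast stays close to the baseline-adjusted completer result.

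In this one scenario, last value carried forward does show the gap. Let c be the mean control change, with 25% of each arm carrying baseline forward: 0.75(c + 0.6) - 0.75c = 0.45 for any c.

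**Is last value carried forward conservative in general?** ANCOVA simulation under these assumptions: 113 per arm, 4,000 runs, true effect zero, about 25% missing per arm, baseline correlation 0.5, mean improvement of 1 SD in both arms, and missingness related to outcome in SHUTi only. The nominal rejection rate is 1.67%.

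| SHUTi missing worse than SHUTi observed by | Completer bias towards SHUTi (rejection) | LOCF bias towards SHUTi (rejection) |
|---|---|---|
| 0 | 0 (1.9%) | 0 (1.8%) |
| about 0.48 SD | 0.09 SD (4.4%) | 0.05 SD (2.3%) |
| about 0.86 SD | 0.16 SD (11.9%) | 0.08 SD (4.4%) |

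So it is not conservative in general.

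**Time 4.** Large-sample simulation under these assumptions: baseline to follow-up correlation 0.5, Time 2 to Time 4 correlation 0.6, true effect 0.60 SD, and about 20-25% dropout after Time 2. The log-odds of dropout depend on Time 1-2 change; a positive slope means that those who improved less leave more often.

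| Slope in SHUTi / control | Completer ANCOVA | Analysis using observed Time 2 |
|---|---|---|
| 1 / 0 | 0.68 | about 0.60 |
| 0.5 / 0 | 0.64 | about 0.60 |
| 1 / 1 | 0.58 to 0.61, depending on the loss in each arm | about 0.60 |

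**Sample size after the fix.** At alpha 0.0167 and an effect of 0.6, power is 93% with the information of 85 per arm and 98% with 113 per arm. If the all-randomised effect is 0.45, power is 70% and 83% respectively.

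**The case against.** The strongest defence is that the protocol chooses efficacy over effectiveness openly, pursues every allocated participant, expects lower attrition than it plans for, and backs the completer result with two sensitivity analyses. Non-adherers who supply data stay in their assigned arm, so the contrast is still by arm, and the ANCOVA is unbiased if missingness depends only on arm and modelled covariates. All of this limits the size of the problem. It does not make the set per-protocol, nor match it to the hypotheses.

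A reader might infer several stronger points that the protocol does not support:
- *That the completer estimate must favour SHUTi.* The document gives no arm-specific dropout pattern. With the same response-dependent dropout in both arms, the Time 4 estimate can fall slightly below the truth.
- *That promoting the mixed model would turn 0.60 into 0.45 at Time 2.* It would not, for the reason shown in the working.
- *That anyone who misses Time 2 is lost to Hypotheses 1.2 and 1.3 even if they return.* This is only one reading. Table S1 also titles Times 3 and 4 as post-intervention assessments, so the exclusion may refer to the visit being analysed.
- *That the undefined word consistent, or the inconclusive rule, is itself a defect.* A criterion may stand in a statistical analysis plan that is not shown, and the rule guards against claiming success on completers alone.

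**Conclusion.** The point holds as a mislabelled primary set and a mismatch between that set and the hypotheses. Both follow from the text without any assumption about dropout.

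The bias is a risk, and its size depends on assumptions. For Time 4 the illustrated range is 0.58 to 0.68 SD against a truth of 0.60. It rests on assumed correlations and on dropout driven by Time 1-2 change, and there the all-available-data analysis does better. For Time 2, 0.45 or 0.53 SD in place of 0.60 rests on an untestable assumption about people who were not observed. No choice of primary model settles that, and the planned last-value-carried-forward analysis reveals it only in that particular scenario. It needs a dedicated sensitivity analysis.

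**What to change.** 1. Define the primary set as all randomised participants, analysed as assigned.
2. Make the planned mixed-effects model primary, using all available visits, with group-by-time terms and the randomisation stratum (suicide attempt history). The Time 2, Time 3 and Time 4 contrasts then test Hypotheses 1.1, 1.2 and 1.3.
3. Keep the ANCOVA as a supportive analysis and label it completers, not per-protocol.
4. Replace or supplement last value carried forward with delta-adjusted or control-based imputation, as the sensitivity analysis for missing Time 2 outcomes.
5. Keep the inconclusive rule, but reword it to name the new sensitivity analysis, since the mixed model it now refers to would become primary.

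The cost is an amendment to the plan's wording and a little more analysis. No new data are needed, and no extra participants to detect an effect of 0.6. The reported effect may be smaller than the completer figure.

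As it stands, the protocol names one population in its hypotheses and analyses another under a label that fits neither.

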***Primary Outcome Measure:***

*Insomnia Severity Index (ISI)* [46]*.* The ISI is a seven-item index of subjective sleep difficulty. Respondents provide information on difficulty with sleep onset, sleep maintenance, and early morning awakenings, as well as interferences with daytime functioning, how noticeable sleep problems are to others, distress caused by problematic sleep, and overall sleep satisfaction. Total scores range from 0 to 28 with higher scores indicating greater insomnia severity. The ISI is a reliable, valid measure that can be delivered through the Internet [62] and is sensitive to changes in insomnia treatment studies [46]. The suggested guidelines for interpretation are: 0-7 = no clinically significant insomnia; 8-14 = subthreshold insomnia; 15-21 = clinical insomnia of moderate severity; 22-28 = severe clinical insomnia.

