***Secondary Outcome Measure:***

*The Veteran’s SF-36 (VA SF-36)* [63]: The VA SF-36 is the primary measure of health-related quality of life used within VA populations, built on the Medical Outcomes Study (MOS) SF-36 [64]. The Veteran’s SF-36 measures eight concepts of health, with two summary scores: physical component summary and mental component summary.

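### The protocol gives two definitions of its primary outcome, and sets no familywise control for the six formal tests at six months and one year

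*Protocol*

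**What the plan says.** Section IV.A of the protocol has a singular heading, "Primary Outcome Measure", with only the ISI under it. The Veteran's SF-36 follows under "Secondary Outcome Measure", described as an instrument "with two summary scores: physical component summary and mental component summary".

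The Analysis Plan in section IV.F ranks them differently. For Hypothesis 1.1 it calls the between-group comparisons of change in ISI, PCS and MCS the primary analyses, and bases inference on the group coefficient "in each of three analysis of covariance models with the change from Time 1 to Time 2 for each outcome serving as the dependent variable". It then fixes the level: "To control for the three primary comparisons, the significance level will be set to 0.0167".

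The Sample Size text assumes the same 0.0167 under a Bonferroni correction, and also invokes "the Horn sequential procedure" to control familywise error. The Analysis Plan does not mention that procedure.

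For Hypotheses 1.2 and 1.3 the Analysis Plan applies a similar analysis to the same three outcomes at Time 3 and Time 4 and gives no level. Its general rule is: "All analyses will assume a two-sided test of hypothesis and a significance level of 0.05, unless otherwise noted". Section I states Hypotheses 1.2 and 1.3 in the same form as 1.1, as predictions of a significant difference. Only Objective 1.4 is labelled exploratory.

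**The concern.** The outcome section and the analysis section cannot both stand. A trial with one primary outcome and a trial with three under an alpha split can reach different conclusions from the same data. The choice should be fixed before the data are seen. A separate statistical analysis plan could not settle it quietly, because whichever way it went it would contradict one section of the protocol.

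The persistence claims raise a second matter. They are formal hypotheses on three outcomes at two times, yet the only multiplicity statement is tied to the three Time 2 comparisons. A significant result on any one of the six could be reported as confirming persistence, with a false-positive risk that nobody has set.

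**Working it through.** **The protocol's own level.** Three comparisons at familywise 0.05: 0.05/3 = 0.01667, which reproduces the stated 0.0167. With three independent tests the familywise error is 1 − (1 − 0.0167)³ = 1 − 0.9507 = 0.049, and the Bonferroni bound is 3 × 0.0167 = 0.050. Hypothesis 1.1, taken alone as three primaries, is therefore controlled.

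**Size of the family.** The Sample Size text speaks of nine outcomes for Hypothesis 1.1, names three, and uses 0.05/3. For nine tests the level would be 0.05/9 = 0.0056. Three outcomes at Times 2, 3 and 4 do make nine tests, but the protocol does not say that this is the source of the number.

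**Two definitions of success.** Take an ISI p-value of 0.03 at Time 2.
- ISI as sole primary at the default level: 0.03 < 0.05, success.
- ISI as one of three primaries at the fixed level: 0.03 > 0.0167, failure.
- ISI as one of three under a Holm step-down (ordered thresholds 0.05/3 = 0.0167, 0.05/2 = 0.025, 0.05): success if the other two p-values have already passed 0.0167 and 0.025, otherwise failure.

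The last line also shows why a fixed 0.0167 gives something away. Holm rejects everything that fixed Bonferroni rejects, and sometimes more, at the same familywise level.

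**Hypotheses 1.2 and 1.3.** Three outcomes × two times = six tests. Both readings of the missing level are shown. If all nulls are true and the tests are independent, the chance of at least one false positive is 1 − Π(1 − αᵢ). The correlated figures come from simulating 300,000 sets of normal statistics with one common correlation. The protocol gives no correlations, so 0.3, 0.5 and 0.7 are assumptions.

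| Tests | Formula | Independent | r = 0.3 | r = 0.5 | r = 0.7 |
|---|---|---|---|---|---|
| Six at 0.05 | 1 − 0.95⁶ | 0.265 | 0.24 | 0.21 | 0.16 |
| Six at 0.0167 | 1 − 0.9833⁶ | 0.096 | 0.09 | 0.08 | 0.06 |
| All nine at 0.0167 | 1 − 0.9833⁹ | 0.141 | 0.13 | 0.11 | 0.08 |
| Three at 0.0167, six at 0.05 | 1 − 0.9833³ × 0.95⁶ | 0.301 | 0.27 | 0.22 | 0.17 |

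The Bonferroni bounds are 6 × 0.05 = 0.30 for the first row, 9 × 0.0167 = 0.150 for the third, and 3 × 0.0167 + 6 × 0.05 = 0.350 for the last.

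**What the alpha split costs the ISI.** Inputs from the Sample Size text: 85 per group, effect size 0.6, two-sided two-sample t-test. Degrees of freedom are 2 × 85 − 2 = 168, and the noncentrality is 0.6 × √(85/2) = 3.91.
- At 0.0167: critical t = 2.417, power 93.1%.
- At 0.05: critical t = 1.974, power 97.3%.
- At 0.05/9 = 0.0056: critical t = 2.809, power 86.3%.

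The stated 80% per outcome does not reproduce from these inputs. That is a separate matter and does not bear on this point.

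**The case against.** The strongest reply is that Objective and Hypothesis 1.1 in section I cover insomnia symptoms and physical and mental functioning together. Three Time 2 comparisons under Bonferroni follow that aim and validly control its error. This stands. The three-primary design is legitimate, and making the ISI the sole primary is a choice for the sponsor. It does not remove the conflict with the labels in section IV.A.

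Second, no sentence sets 0.05 for Times 3 and 4. That level is inferred from the default rule, and a similar analysis described shortly after the 0.0167 sentence may be meant to inherit 0.0167. This also stands, so 26.5% cannot be given as the plan's error rate. Under the milder reading the nine tests as one family still have a bound of 0.150.

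Third, the protocol calls a hypothesis inconclusive when a mixed-effects sensitivity analysis disagrees. That is a consistency check on overlapping data. It does not control error across outcomes and times.

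Some stronger inferences are not supported:
- A reader might conclude that a PCS gain alone would count as trial success. An alpha split is compatible with such a rule, but no section states it, and Hypothesis 1.1 joins the outcomes with an "and"-type wording.
- A reader might conclude that the split costs the ISI about ten points of power. That needs an effect size of 0.5. At the protocol's 0.6 the loss is 97.3 − 93.1 = 4.2 points.
- A reader might say that the sample size rests on a sequential procedure and the analysis on Bonferroni. The Sample Size text names both, so part of the inconsistency lies within that paragraph.

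**Conclusion.** The point holds in two parts.

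The conflict over the primary outcome is explicit in the text and rests on no assumption. It changes the outcome of the trial whenever the ISI p-value at Time 2 falls between 0.0167 and 0.05. Its cost in power is modest at the planned effect size.

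The missing control for Hypotheses 1.2 and 1.3 holds on either reading of the unstated level, but its size depends on which is meant. For the six tests it is 16% to 26.5% at 0.05, and 6% to 10% at 0.0167. All nine at 0.0167 give 8% to 14%. Each range runs from an assumed correlation of 0.7 down to independence, with all nulls true.

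The fixed 0.0167 is valid, but it is no more powerful than a step-down test at the same familywise level and leaves unused the sequential approach that the Sample Size text already names.

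**What to change.** 1. **Make section IV.A and the Analysis Plan agree.**
   - If three primaries are kept, relabel the SF-36 summary scores in section IV.A and test the three Time 2 comparisons by a Holm step-down at familywise 0.05 in place of fixed 0.0167.
   - If the ISI alone is primary, test it at two-sided 0.05 at Time 2, and test everything else in one valid sequence after it succeeds, for example Holm at 0.05 over the remaining eight tests.

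2. **Avoid parallel spending.** Do not open the ISI at Time 3 at 0.05 alongside PCS and MCS at Time 2 at a further 0.05. If only the ISI effect at Time 2 is real, that gives 1 − 0.95 × 0.975² = 9.7% familywise error with independent tests.

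3. **State the status of Times 3 and 4.** With three primaries, either run Holm across the three outcomes at Time 3 only if all three succeeded at Time 2, and likewise for Time 4 after Time 3, or run Holm over all nine tests. With either choice of primary, the alternative is to say that the Time 3 and Time 4 tests are supportive and carry no familywise control.

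4. **Name one multiplicity procedure** in both the Sample Size text and the Analysis Plan.

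The cost is an amendment and a stricter or conditional threshold for later or SF-36 claims. Choosing the ISI alone also re-ranks the outcomes that Hypothesis 1.1 puts together, so it is more than a wording change. Even at 0.0056, the strictest step of Holm over nine, power is 86.3% at an effect of 0.6 with 85 per group. Applying that figure to Times 3 and 4 assumes 85 per group are still evaluable there; the protocol ties its 25% attrition to the post-intervention assessment.
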